## Abstract

**Background:**

Violence against children in schools is a global public health problem. There is growing evidence that school-based interventions can be effective in reducing violence against children in schools. However, there is little evidence on the long-term impact of such interventions. The Good School Toolkit, developed by Raising Voices, a Uganda-based nonprofit organization, is a whole-school violence prevention intervention that aims to change the operational culture of primary schools. In 2014, the Good School Toolkit was evaluated through a cluster randomized controlled trial (Good Schools Study) and found to reduce teacher-to-student and student-to-student violence.

**Objective:**

This protocol describes quantitative analyses to explore long-term outcomes of the Good School Toolkit intervention among adolescents in Uganda, including the extent to which it is associated with peer-violence victimization (primary outcome) and peer-violence perpetration, intimate-partner violence, acceptance of teacher-violence, equitable gender attitudes, agency, self-regulation, peer connectedness, social assets, psychological assets, and retention in school (secondary outcomes).

**Methods:**

This is a nonrandomized quasi-experimental 4-year follow-up study of adolescents who attended the 42 Good Schools Study primary schools in 2014; 21 schools initiated the Good School Toolkit intervention during the trial from 2012, and 19 schools initiated the intervention after the trial (during the later delivery phase) from 2015; 2 schools did not implement the intervention. Students in the final school grade (Primary 7) during 2014 of the 19 primary schools in the later delivery phase are expected to have left school prior to toolkit delivery in 2015. Wave 1 data were collected in 2014 from 3431 grade Primary 5 to Primary 7 school students aged 11-14 years; these students were followed up in 2018-2019 when aged 16-19 years and invited to participate in the Wave 2 survey. Data were collected in face-to-face interviews by trained Ugandan field researchers. Toolkit exposure groups are defined as exposed during the Good Schools Study trial (from 2012), as exposed during later delivery (from 2015), or not exposed including those expected to have completed Primary 7 prior to later delivery or from the 2 schools that did not implement the toolkit. Associations between outcomes at Wave 2 and toolkit exposure groups will be analyzed using mixed-effect multivariable logistic and linear regression models for binary and continuous outcomes, respectively. This analysis is exploratory and aims to generate hypotheses on if, and under what circumstances, the toolkit influences later adolescent outcomes.

**Results:**

Data collection was completed in August 2019.

**Conclusions:**

To our knowledge, this is the first long-term follow-up study of adolescents exposed to a school-based violence-prevention intervention in sub-Saharan Africa. If the intervention reduces violence and improves other outcomes in later adolescence, then this study supports primary school interventions as key to achieving long-term population impacts. The pattern of effects will inform where reinforced or additional interventions are needed.

**International Registered Report Identifier (IRRID):**

DERR1-10.2196/20940

## Introduction

### Background

Globally, over 1 billion children experience violence every year [1]. In Uganda, 75% of 18- to 24-year-old individuals report violence in their childhood [2], and over half of ever-married women report physical violence from an intimate partner in their lifetime [3]. Violence against children that occurs in school is a global public health problem that takes many forms. It may include physical, emotional, and sexual violence and involve different perpetrators and power dynamics [4]. In Uganda, similar to in other resource-constrained settings, the majority of primary school students have experienced physical violence from a teacher, and almost half have experienced physical, emotional, or sexual violence from a fellow student [5-7]. Negative health, social, and economic outcomes among those who experience violence in childhood have been well described [8]. Furthermore, experiencing violence as a child may lead to a “cycle of violence” with increased aggressive behavior and greater risk of boys perpetrating violence and girls experiencing intimate-partner violence later in life [9]. Uganda’s Demographic and Health Survey 2016 indicated that, nationally, 84% of primary school–aged children attend some primary school [3], and 60% of those who complete primary school transition to secondary education [10]. The extent and consequences of violence call for urgent effective violence prevention strategies that can protect against childhood violence and reduce the risk of future violence by supporting positive transitions through adolescence into adulthood [11,12].

### Long-Term Effects of School-Based Violence Prevention Interventions

Evidence from high-resource settings suggest that some school-based violence-prevention interventions show promising long-term effects on violence outcomes 3 or more years later [13,14]: Safe Dates, delivered to the eighth-grade students in the United States, reduced dating violence 4 years later [15]; Learning Together, in UK secondary schools, reduced bullying victimization at 36 months [16]; Gatehouse Project, a social-inclusion intervention in Australian secondary schools, reduced risky behavior (a composite measure that included interpersonal violence) after 4 years [17]; Aban Aya Youth Project, a social-emotional program delivered to Grade 5 to 8 students in the United States, reported a reduced rate of increase in violent behavior among boys over 4 years [18]; and Positive Action, a multiple-risk behavior intervention in Hawaii and US eliminatory schools, which reported reduced violent behavior after 3 to 6 years [19,20]. The majority of these interventions have been delivered in secondary schools through a variety of approaches, and outcomes are assessed when students are still in school [13]. Effective pathways from primary school interventions to long-term violence reductions are less understood in resource-constrained contexts. To our knowledge, no whole-school intervention that acts on reducing teacher-to-student violence has been evaluated in terms of long-term impacts after adolescents transition out of primary school.

### The Good School Toolkit Intervention

The Good School Toolkit, a violence against children–prevention intervention, was developed by Ugandan nonprofit organization Raising Voices and is freely available for download on their website [21]. It is a complex school-wide intervention that addresses multiple actors and behaviors and was designed to be locally adapted. The intervention is school-led through 2 appointed teacher and student protagonists. Materials are provided along with over 60 interactive and accessible activities that engage the whole school as they sequentially complete the 6 core steps (Textbox 1).

Good School Toolkit steps [21].Step One: Your Team & NetworkSchools identify key protagonists at school and create their Good School Committee to build school-wide support for the process (precontemplation)Step Two: Preparing for ChangeBaseline measurements gather information on each schools’ starting point, and school leaders cultivate interest among parents, the community and local education officials (contemplation)Step Three: Good Teachers & TeachingA school-wide reflection on teacher-student relationships provides a renewed sense of teacher roles, increased professional support, and new approaches for positive student engagement (preparing for action)Step Four: Positive DisciplineSchools reflect on how violence manifests and establish a new school culture by exploring positive disciplinary methods to create students who believe in themselves (action).Step Five: Good Learning EnvironmentSchools reflect on what a good learning environment looks like and work with all stakeholders to foster a psychological sense of safety and inclusion (maintenance of action)Step Six: Good Administration & the FutureThe work of the preceding steps is celebrated and consolidated through reflection and transfer of leadership to the school administration (consolidated gains)

Figure 1 summarizes the toolkit programmatic theory of change [22]. The intervention aims to positively transform operational culture within primary schools. Raising Voices conceptualizes school operational culture as consisting of 3 domains drawn from Moos’ [23] interpretation of the social-ecological framework: (1) psychological, referring to attachment, belonging, identification with—and attitudes toward—the school; (2) relational, referring to interpersonal relationships between teachers and students and between students; and (3) structural, referring to policies, administrative infrastructure, and capacity [24].

**Figure 1 figure1:**
[figure not shown]
Good School Toolkit programmatic theory of change.

The Good School Toolkit is one of the few school interventions with a demonstrated impact of reducing school violence in a resource-constrained setting, including teacher-to-student violence [25]. The Good Schools Study included a cluster randomized controlled trial [26,27], qualitative study [28], process evaluation [29], and economic evaluation [30]. During the trial, conducted in Luwero district in Uganda from 2012-2014, the toolkit was delivered to 21 intervention schools that were compared with 21 wait-list control schools. The trial found that the toolkit reduced the relative risk of past-week teacher-to-student physical violence by 42% [27]. Secondary trial analysis found that the toolkit reduced teacher-to-student past-week physical, emotional, or sexual violence (adjusted odds ratio [OR] 0.41, 95% CI 0.26-0.64) and any student-to-student past-week physical, emotional, and sexual violence (adjusted OR 0.70, 95% CI 0.51-0.96) [31,32]. Subsequently (from 2015), the toolkit was delivered to 19 of the wait-list control schools. While the intervention remained the same (see Table 1), during later delivery the intervention was implemented by *resource persons*, trained and supported by Raising Voices, rather than the Raising Voices program team.

**Table 1 table1:** The Good School Toolkit intervention delivered during the trial and later delivery to study schools.

TIDieR [33] guideline	Description of the toolkit
Brief name	Good School Toolkit
Why	The goal of the toolkit was to transform the operational culture at the school level such that violence against children is prevented. The toolkit draws on the Transtheoretical Model [34] and contains behavior change techniques that have been shown to be effective in a variety of fields [35] and have been included in interventions to change teacher behavior in primary schools [36,37] and reduce perpetration of intimate partner violence [38].
What-materials and content	The toolkit materials consist of books, booklets, posters, and facilitation guides for about 60 different activities. These activities are related to creating a better learning environment, respecting each other, understanding power relationships, using nonviolent discipline, and improving teaching techniques. All materials are publicly available online. Specific behavior change techniques for staff, students and administration included setting school-wide goals, developing action plans with specific dates for deliverables, encouraging empathy by facilitating reflection on experiences of violence, providing new knowledge on alternative nonviolent discipline, and providing opportunities to practice new behavioral skills. Schools were encouraged to self-monitor their progress according to their action plans. Reinforcement of new information and ideas, feedback on progress, and modeling of new techniques and behaviors were provided by visits from the Raising Voices team and also within the school by protagonists to their peers as they gained new knowledge and skills. Children actively participated and formed committees and groups related to different activities. Schools rewarded the successful achievement of their goals and action plan deliverables by creating celebrations. Social support for behavior change was also created because the intervention engaged multiple groups within a school (teachers, administration, students, and also parents) to change ideas and attitudes.
What-procedures	Following a school’s agreement to participate, an inception visit of 2 hours was held, where Raising Voices introduced the toolkit to all school staff. Once the schools were committed to implementing the toolkit, at least 2 staff protagonists were identified who attended a 3-day residential workshop. During this workshop, the protagonists became familiar with the toolkit and developed an action plan for their school. Raising Voices staff members then provided direct one-on-one support and mentorship to key staff protagonists students and at least 2 key student protagonists in each school to carry out the action plan. The toolkit itself has 6 steps, which were designed to be implemented in sequence to guide schools through a systematic process of change. Protagonists could choose which activities they implemented but should complete a minimum number from each step before moving on to the next.
Who provided	Delivery to trial schools: Raising Voices program staff members were trained facilitators and advocates and had received approximately 100 hours of training with individualized coaching support to understand the ideas and content of the toolkit. Later delivery to schools: Raising Voices resource persons were experienced consultants, usually working within the education sector who received at least 20 hours of training and then subsequent individualized coaching support by Raising Voices program staff to understand the ideas and content of the toolkit and how to provide support to school-based protagonists. The key protagonists in each school were 2 teachers who receive 3-day residential workshop based training and ongoing support.
How	During the intervention, Raising Voices staff or resource persons provided direct one-on-one support in the form of in-person visits and telephone calls to staff protagonists, and in-person visits to student protagonists. Staff and student protagonists conducted face-to-face activities with other staff and students in their school, mainly in groups. Children and staff members encouraged others to form, lead, and join groups for various intervention activities.
Where	Activities with students and staff were conducted in schools. Some activities involved creating a better school environment by painting murals on school walls and hanging codes of conduct in visible places; however, the intervention does not require any physical infrastructure.
When and how much	Raising Voices staff made in-person visits to protagonists in each school quarterly and telephoned school staff members approximately monthly, although this varied slightly depending on need. The toolkit itself was designed to be implemented flexibly, and there was no prescribed number of activities or set schedule upon which they should be implemented. However, schools should proceed in sequence and conduct a minimum number of activities, which depends on the stage, prior to progressing to the next stage.
Tailoring, modifications, fidelity	The toolkit was specifically designed to be flexible and adaptable to individual schools. To ensure more uniformity during the trial, Raising Voices staff visited each school at least once per school term, conducted a 3-day residential workshop with all teacher protagonists, met with protagonists to review progress after 1 to 2 terms of implementation, and held meetings with protagonists so they could learn from each other.

### Long-Term Effects: Conceptual Framework

A schematic that illustrates mechanisms through which the Good School Toolkit may achieve long-term effects is shown in Figure 2. The Good Schools Study’s quantitative and qualitative findings suggested that the toolkit intervention improved the schools’ operational culture and enhanced student capabilities, including improvements in student-teacher relationships; fostered attitudes that were less accepting of teacher violence; enhanced emotional support from peers; allowed enhanced school-connectedness; and improved self-regulation, voice, and motivation [28,31,39-41]. We hypothesize that students who experienced the toolkit intervention during their primary education (ie, were exposed to a supportive culture and less violence in a safer school environment) are less likely to drop out of school and therefore are retained in the education system for longer. Furthermore, we hypothesize that students’ enhanced capabilities—brought about by the toolkit intervention—can be retained through the transition out of primary school into new environments, equipping adolescents with individual skills supportive of resilience. Through these positive changes brought about by exposure to the toolkit intervention, we hypothesize that adolescents will have attitudes that are less accepting of violence, will be more gender-equitable, and will be less likely to perpetrate or experience peer and intimate partner violence in later adolescent relationships.

**Figure 2 figure2:**
[figure not shown]
Schematic illustrating the toolkit intervention long-term effects conceptual framework.

Adolescents’ interactions within supportive social ecologies are important for both positive development and resilience [39,42]. Environments outside of primary school are also likely to influence adolescents’ trajectories, in particular, family support, economic pressures, and violence experienced outside of school. As adolescents transition out of primary school, experiences in new secondary schools, the workplace, and domestic contexts are expected to affect adolescents’ outcomes. While enhanced capabilities may support Ugandan adolescents in navigating risk of violence and collectively advocate for change, this is largely limited by gender-related vulnerabilities within shifting risk environments [43]. In addition, adolescents’ negotiations and need for support, resources, and services may not be met by family, school, workplace, or the community systems, which are all subject to wider structural factors [44]. Consequently, the economic and sociopolitical contexts, gender norms, and access to safe secondary education or employment are expected to influence adolescents’ opportunities for positive adaptations and agency in Uganda [45].

### Research Questions

We aim to evaluate long-term effects of the Good School Toolkit, specifically whether exposure to the toolkit intervention in early adolescence is associated with (1) less violent relationships in later adolescence, including peer-violence victimization (primary outcome), peer-violence perpetration, and intimate-partner violence victimization among female adolescents and perpetration among male adolescents; (2) lower acceptance of teacher violence and more equitable gender attitudes in later adolescence; (3) factors supportive of resilience in later adolescence (enhanced agency, self-regulation, peer connectedness, and social and psychological assets); and (4) increased retention in school.

## Methods

### Design

The proposed quantitative analysis makes use of the variation in the Good School Toolkit intervention delivery to create a nonrandomized quasi-experimental design, comparing outcomes across levels of toolkit exposure. This analysis is exploratory and aims to generate hypotheses on if, and in what circumstances, the toolkit influences later adolescent outcomes. To better understand how context and structural factors may influence later outcomes, further quantitative and qualitative analysis is planned and will be informed by this analysis.

### Sampling, Intervention Delivery, and Survey Assessments

The original Good Schools Study trial sampling is fully described elsewhere [26]. In summary, we used the 2010 list of 268 government and nongovernment primary schools in Luwero district, obtained from the Ministry of Education. Eligibility criteria were school size (>40 Primary 5 students) and having no existing interventions. Of 151 eligible primary schools that were identified and stratified into 3 groups based on the student male to female ratio (>60% girls, >60% boys, or approximately even), 42 schools were randomly selected proportional to the size of stratum. All selected school headteachers agreed for their school to participate. After the trial baseline survey in 2012, stratified block randomization was used to allocate schools to receive the intervention immediately or to be wait-listed to receive the intervention after the end of the trial (Figure 3). Stratified randomization was used to ensure balance regarding the following key factors: baseline violence, whether the school was urban or rural, and a qualitative assessment of the likelihood of attrition throughout the trial. For both the trial baseline (in 2012) and endline (in 2014), for cross-sectional surveys, a simple random sample of up to 130 Primary 5 to Primary 7 students per school were invited to consent for a survey interview, and if there were <130 Primary 5 to 7 students then all were invited. Figure 2 describes the timing of the Good School Toolkit delivery and survey assessments. The trial baseline survey data were collected across the 42 schools in 2012 (n=3706, 77% survey response). In 2014, after 18 months of Good School Toolkit implementation in the 21 intervention schools, trial endline data were captured across the 42 schools (n=3820, 93% survey response). Of the students surveyed at the trial endline, 90% (n=3431) agreed to be followed up. These individuals constituted our Wave 1 sample for this study and analysis. The Good School Toolkit intervention was subsequently delivered to 19 of the 21 wait-list control schools from 2015, by which time the Primary 7 students were expected to have left primary school, and 2 wait-list control schools declined to implement the toolkit. Wave 1 adolescents were traced, and Wave 2 survey data collected during 2018 and 2019. A full description of data collection procedures and methods for our Wave 2 survey are reported elsewhere [46].

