### Potential Confounders and Effect Modifiers

The following factors have been identified a priori as potential confounders or effect-modifiers to the exposure-outcome relationships of interest: biological sex and the number of meals eaten the previous day (as a proxy for socioeconomic status that is expected to be associated with staying in the study school throughout intervention delivery and associated with later violence outcomes). In addition, and as appropriate for specific exposure-outcome relationships, the following variables have been identified as potential effect-modifiers or confounders measured at Wave 1: school grade, family connectedness, and experiences of violence outside of school [68,69].

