### Regression Analysis Strategy

All analysis is exploratory and hypotheses generating rather than testing. To explore if the intervention influences later outcomes, we will compare across the trial and no exposure groups (1 vs 2.2) and original study arms (1 vs 2) first including all 42 schools and then repeated, dropping the 2 nonimplementation schools. To further explore differences between levels of exposure, we plan to compare between trial and the later delivery groups (1 vs 2.1) and across secondary exposure groupings (Figure 3). We will account for clustering by including original study primary school as a random effect in mixed-effect regression models [71]. Binary outcomes will be analyzed using mixed-effect logistic regression, with effect size presented as odds ratios. Continuous outcomes will be analyzed using mixed-effects linear regression, with effect size presented as mean difference. All unadjusted and adjusted analyses will include baseline school-level mean of outcomes, where available [72]. Adjusted models will additionally include covariates identified as potential confounders. All measures of effect will be presented with 95% confidence intervals and *P* values. Size and direction of effect will be considered along with *P* values when assessing the strength of associations [70]. Appropriate methods will be used to analyze numeric outcomes that are not normally distributed. For example, bias-corrected 95% confidence intervals will be estimated using nonparametric bootstrapping. The presence of effect modification will be assessed by comparing models fitted with and without an interaction term. Likelihood ratio tests with *P* values<.1, along with the direction and size of effect for each group, will be considered as evidence for or against modification. If there is evidence of modification, then stratum-specific effects will be calculated [73].

For self-reported exposure, propensity score–matching will be used to account for the likelihood that self-reported exposure is confounded by an individual’s propensity to report exposure. We will estimate what factors predict toolkit exposure using regression analysis [29], then calculate predicted probability of exposure and group adolescents with similar propensity scores. The analysis will compare outcomes across these propensity score exposure groups, including the score as a covariate in regression models [72].

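### Schools were randomised within strata, but the models carry no urban/rural, attrition-likelihood or stratum term, and baseline violence enters only by proxy; the randomised contrast (1 vs 2) loses precision

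*Protocol article*

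**What the plan says.** On allocation, the section Sampling, Intervention Delivery, and Survey Assessments says that "stratified block randomization was used to allocate schools to receive the intervention immediately or to be wait-listed". It names two of the factors as follows: "Stratified randomization was used to ensure balance regarding the following key factors: baseline violence, whether the school was urban or rural". The third factor is described there as "a qualitative assessment of the likelihood of attrition throughout the trial".

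On analysis, the section Regression Analysis Strategy plans both a non-randomised and a randomised contrast: "we will compare across the trial and no exposure groups (1 vs 2.2) and original study arms (1 vs 2) first including all 42 schools". The model content is stated in three steps:

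- Clustering: "We will account for clustering by including original study primary school as a random effect in mixed-effect regression models".
- Baseline: "All unadjusted and adjusted analyses will include baseline school-level mean of outcomes, where available".
- Adjustment: "Adjusted models will additionally include covariates identified as potential confounders".

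The section Potential Confounders and Effect Modifiers supplies the covariates. They are "biological sex and the number of meals eaten the previous day" and, as appropriate to the relationship, school grade, family connectedness and violence outside school, all from Wave 1. Neither section mentions urban/rural status, the attrition rating or a stratum indicator.

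**The concern.** An analysis of a stratified randomisation should reflect the strata. Stratifying makes the arms alike on the chosen factors, so the true sampling variance of the arm difference is smaller than under simple randomisation. A model without those factors does not see this. It counts between-stratum differences among schools as unexplained school variation and reports a standard error that is too large.

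With 42 schools, between-school variance is the main limit on precision. The section Principal Findings intends to read an absence of long-term impact as a sign that further efforts are needed, so avoidably wide intervals have a cost even in an exploratory study.

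The gap differs by outcome. For violence outcomes measured in 2012, the school mean stands in closely for the baseline-violence factor. The agency and self-regulation measures were adapted and piloted for the Wave 2 questionnaire, so they appear to have no 2012 mean. If so, their models contain nothing for any of the three factors.

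In 1 vs 2.2 and 1 vs 2.1 the groups are defined partly by grade and are not randomised. Urban/rural status matters there as a candidate confounder, not as a design stratum.

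**Working it through.** **The plan's own figure.** The only power statement (Power to Detect a Difference) concerns 1 vs 2.2: 456 vs 1201 adolescents, 50% in the no exposure group, 80% power, an 8% difference, OR 0.73. With two-sided alpha 0.05, pooled variance under the null and no design effect, the detectable difference d solves

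d = 1.96·√[p̄(1−p̄)(1/456 + 1/1201)] + 0.8416·√[p0(1−p0)/456 + p1(1−p1)/1201].

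This gives 7.7 points, OR 0.734, which agrees with the plan. (Alpha is printed as .5, which would give 4.2 points; that is a separate matter.) The figure belongs to a non-randomised contrast, so it cannot size the present point. The article gives no corresponding figure for 1 vs 2.

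**Inputs for 1 vs 2.** From the article: 2402 adolescents expected in 42 schools, so m = 2402/42 = 57.2 per school. Assumed, because the article does not give them: ICC 0.01, 0.03 and 0.06, and R², the share of between-school variance explained by the strata *beyond* what the baseline outcome mean already removes, at 0.1, 0.3 and 0.5. Equal school sizes and a large-sample linear approximation are also assumed.

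**Formulas.** The variance of a school mean, in units of total variance, is

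- strata omitted: V0 = ICC + (1 − ICC)/m
- strata included: V1 = ICC(1 − R²) + (1 − ICC)/m

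and r = √(V0/V1) is the factor by which omission overstates the standard error. The actual type I error at nominal 0.05 is 2[1 − Φ(1.96r)]. If power is 80% with the strata in the model, it is Φ(2.8016 − 1.96r) without them.

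**Example.** At ICC 0.03, (1 − 0.03)/57.2 = 0.0170 and V0 = 0.0470. At R² = 0.1, V1 = 0.0270 + 0.0170 = 0.0440 and r = 1.034. At R² = 0.5, V1 = 0.0150 + 0.0170 = 0.0320 and r = 1.212.

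| ICC | R² | SE ratio r | Type I error | Power if 80% with strata |
|---|---|---|---|---|
| 0.01 | 0.1 | 1.019 | 0.0458 | 79.0% |
| 0.01 | 0.3 | 1.060 | 0.0378 | 76.6% |
| 0.01 | 0.5 | 1.106 | 0.0301 | 73.7% |
| 0.03 | 0.1 | 1.034 | 0.0428 | 78.1% |
| 0.03 | 0.3 | 1.112 | 0.0293 | 73.3% |
| 0.03 | 0.5 | 1.212 | 0.0175 | 66.5% |
| 0.06 | 0.1 | 1.042 | 0.0412 | 77.6% |
| 0.06 | 0.3 | 1.144 | 0.0250 | 71.2% |
| 0.06 | 0.5 | 1.283 | 0.0119 | 61.3% |

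**On the percentage-point scale.** Take ICC 0.03, 1201 per arm and, as a further assumption, the plan's 50% for the whole wait-list arm. The design effect is 1 + (57.2 − 1) × 0.03 = 2.69, the effective size per arm is 1201/2.69 = about 447, and the detectable difference without strata is about 9.3 points. With strata it is 9.3/1.034 = 9.0 points at R² = 0.1 and 9.3/1.212 = 7.7 points at R² = 0.5.

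**The case against.** The strongest reply is that the factor closest to the outcome is already covered. Every model, including those called unadjusted, carries the 2012 school mean where available, and for violence outcomes this is arguably finer than a stratum. That stands. It means R² must be read as what is left after that adjustment, and the lower rows of R² may be the realistic ones.

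Second, the error is conservative and the analysis is declared exploratory, with size and direction of effect weighed alongside P values. That also stands, and it limits the importance of the point.

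Third, an article may leave covariate detail to an analysis plan. This stands only in part. The article does fix the random effect, the baseline term and an a priori confounder list, and the point is about that stated content. A fuller plan may already include the strata.

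Three stronger readings are tempting but not supported:

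- *Urban/rural imbalance biases 1 vs 2.2.* No imbalance is shown. Group 2.2 draws on all 21 wait-list schools (Primary 7 in 19, all surveyed grades in the 2 that declined), so balance across schools should largely carry over. It could be disturbed because those 2 schools contribute more grades, but that is only a possibility.
- *The attrition rating predicts the loss of about 30%.* The rating concerned the trial period, nothing links it to tracing in 2018-2019, and 70% follow-up is a planning assumption. Differential attrition has its own checks in the Analysis Plan section.
- *The omission could produce false positives.* For 1 vs 2 the direction is the opposite.

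**Conclusion.** The point holds as one of efficiency for the randomised contrast. Two of the three randomisation factors appear in no model, and the third appears only by proxy and only where a 2012 mean exists. For 1 vs 2 the standard error is overstated by about 2% to 28%, actual type I error falls to between about 0.046 and 0.012, and 80% power becomes about 61% to 79%. These ranges rest on the assumed ICC (0.01-0.06) and residual variance explained (10-50%). If the strata add little beyond the baseline mean, the loss is at the small end.

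For 1 vs 2.2 and 1 vs 2.1 the finding is narrower. A known pre-allocation school characteristic is absent from the confounder list, although the Limitations section names confounding as a concern and promises control of observed confounders. The documents do not show that bias results.

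**What to change.** For 1 vs 2, add the randomisation strata as school-level fixed effects in both the unadjusted and adjusted models. Alternatively, add urban/rural status and the attrition-likelihood rating, plus baseline school violence for outcomes without a 2012 mean. Use the same terms in the repeat that drops the 2 non-implementing schools, since balance is no longer assured there. For 1 vs 2.2 and 1 vs 2.1, add urban/rural status to the a priori confounder list. If any of these factors is left out on purpose, say why.

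The cost is small. The factors must have been recorded to carry out the allocation, though the Data Management section does not name them among the data to be merged; a file with one row per school would suffice. The statistical cost is a few between-school degrees of freedom: 42 schools less 2 arms leaves 40, the baseline mean takes 1, and two binary terms would leave 37. The number of strata and the levels of the attrition rating are not stated. If a full set of stratum indicators would be large, the separate factors are preferable, and the number of school-level terms should be kept small. The Results section says that analysis had not been done, so the change could still be prespecified when the article was written.
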